## Abstract

**Background:**

Motor vehicle crashes and resultant fatalities remain disproportionately high among young drivers, with crash risk peaking immediately after licensure. Although graduated driver licensing laws (GDL) for young novice drivers have reduced such fatalities, driver error remains a leading cause; thus, prevention efforts that target improving skills in novice teen drivers *before* licensure are a strong candidate for reducing crash risk early in licensure. States with more comprehensive driver licensing laws that include mandated driver training before licensure in addition to GDL show lower crash rates post-licensure, but these effects were not determined through rigorous controlled studies of driver training. This paper describes the DRIVER study, a phase III randomized trial that tests the effectiveness of two different driver training programs in reducing young driver crash risk early in licensure in Pennsylvania, a state like many others that does not require formal training for young drivers.

**Methods:**

Learner drivers age 16 and 17 years will be recruited and followed through the GDL learner phase and for six months post-licensure. Participants will be randomly assigned to one of three interventions: professional behind-the-wheel training (n = 333), online hazard training (n = 333), or an active control online vehicle and driver safety course, unrelated to hazard skills training (n = 333). The primary outcomes are on-road crash risk post-licensure (via kinematic hard braking events tracked through a smartphone-based app) and state license examination performance. Secondary outcomes include change in simulated driving performance from baseline to the time of license examination, self-reported and kinematically tracked risky driving behavior (e.g. cell phone use, speeding) and self-reported crashes. Participants will complete baseline surveys and cognitive assessments to determine potential moderating effects of cognitive maturation and risk-taking tendencies.

**Discussion:**

Findings from the DRIVER study will provide insights into training effectiveness generally, and an evidence base for recommendations to policy makers, while also revealing for whom these interventions are less effective.

**Trial registration:**

The study was registered on ClinicalTrials.gov Registry (NCT06413927) in May 2024, https://clinicaltrials.gov/study/NCT06413927 and last updated on August 11th, 2025. This protocol was developed per the SPIRIT (Standard Protocol Items: Recommendations for Interventional Trials) Checklist.

## Introduction

Motor vehicle crashes remain a leading cause of death and injury worldwide, with children and young people most at risk [1]. In the US, young drivers are overrepresented in crashes [2, 3], with long-term sequela including chronic disabilities leading to ongoing medical care, reduced workforce participation, and disability-related costs [4]. The US adopted graduated driver licensing laws (GDL) as the national strategy for reducing young driver crash risk. At a minimum, US GDL requires a learner permit period and restricted driving conditions during an intermediate or junior license [5, 6]. Yet, despite GDL, young driver crashes remain high [7]. Typically, crash risk peaks within the first 2–3 months after licensure, and then lowers to adult levels between 1.5–2 years post-licensure [8, 9]. Furthermore, driver error, due to a lack of skills and experience [10], accounts for approximately 76–94% of crashes [11, 12]. Thus, prevention efforts that target improving skills *before* licensure are promising strategies for reducing crash risk early in licensure.

Recent studies suggest that behind-the-wheel driver training (BTW) may improve safety early in licensure [9, 13]. In Ohio, a state that mandates driver education and BTW in addition to GDL for drivers under age 18 years, these young drivers had better skills at licensure and lower crash rates early in licensure, relative to those licensed at age 18 years (without BTW) [13]. Similar policies and lower crash rates have been observed in California [9]. While these studies were not randomized trial studies, and could not account for exposure (i.e. varying time spent on the road), they show some promise that skills training before licensure may be a modifiable risk factor. However, a 2022 review of state policies found that 17 states (including Pennsylvania) have no BTW requirements for young drivers, with an additional 3 states allowing for BTW to be replaced (e.g. with adult supervised practice) [14].

State endorsement of BTW for licensure has dwindled since the 1980s, since the only random assignment study of BTW to date (the DeKalb study, 1983) [15] found modest short-term protective effects of BTW on 6 month outcomes, but concluded it did not reduce crashes overall [15, 16]. The most rigorous re-analysis of these data showed a 13.1% crash reduction in the first 6 months of licensure (which we now know is the period of highest lifetime crash risk [8, 17]). Prior research shows that skill deficits underscore most of these early crashes, pointing to the potential value of training [10, 11, 18–20]. While the DeKalb study was rigorous in its random assignment design, it did not capture exposure, and predates modern GDL, vehicle safety, driver training standards, as well as modern risks (e.g. cell phone use). Therefore, there is a critical need for a contemporary examination of the effectiveness of driver training for improving young driver safety in the US.

The DeKalb study also did not account for other known individual risk factors, such as cognitive development and impulsive traits. Even among typically developing youth, executive function and attentional skills, and associated brain regions, show dramatic maturation during adolescence (when many adolescents learn to drive) before stabilizing by age 18–19 or later [21]. These executive functions, particularly working memory, have been linked to driving performance and outcomes in young drivers [22–25]. Risk-related impulsive personality traits that peak in adolescence in association with executive function have also been associated with crash risk [26–29]. However, we hypothesize that sufficient skills training may offset developmental risk factors, given the youngest new drivers in Ohio who completed driver training had the lowest crash rates [13].

Despite the potential benefits of BTW, access is uneven due to cost and location barriers [14, 30]. Alternatively, validated digital training programs for improving safety–critical skills and reducing crashes have the potential to overcome these barriers. Specifically, three free virtual training programs in hazard awareness and mitigation (RAPT and ACT) [31–33], and attention maintenance skill training (FOCAL) [34] have been packaged as an omnibus driver education program (ACCEL) [35] that has shown promise in licensed young novice drivers [36]. Online driver's education programs can eliminate the need for travel to a physical driving school, benefiting individuals in remote or rural areas where access to such facilities is limited. However, this intervention has not been tested in the pre-licensure phase for efficacy in reducing crash risk post-licensure.

### Objectives

The primary objective of the DRIVER (DRIVer Education Research) study is to quantify the extent to which modern online driver training and BTW prior to licensure can add protection beyond GDL against crash risk early in licensure. The secondary objective is to quantify the effect of driver training on skill acquisition. The study aims and outcomes are summarized in Table 1. We hypothesize that both ACCEL and BTW training will reduce crash risk and improve driving skills compared to the control group. More specifically, we hypothesize that ACCEL will show greater improvement in crash risk and skills than BTW on the theory that ACCEL is more targeted to the critical reasons for crashes among novice adolescent drivers. However, we expect BTW to perform better on PA license examination outcomes since this test measures skills directly trained by BTW. We also hypothesize that those with weakness in cognitive and attentional control will benefit most from the training interventions in the key outcomes, and those with personality differences and risky driving practices linked to crash risk may be more resistant to the effects of driver training.

**Table 1 Tab1:** Summary of study aims and associated outcomes

Study Aim	Primary Outcome	Secondary Outcome
**Aim 1**. Determine the effect of driver training (ACCEL or BTW) compared to GDL alone on post-licensure crash risk	Hard Braking Events per 100 miles driven via Way to Drive monitoring app	• Phone Use while Driving (minutes per hour of driving) • Speeding (proportion of time > 10 miles over posted speed limit) • Self-reported crash involvement • Self-reported risky driving behavior
**Aim 2**. Determine the effect of driver training (ACCEL or BTW) compared to GDL alone on skill acquisition	Pass rate on the first attempt at the state licensing examination	• Virtual Driving Assessment (VDA) Performance at T2 • Change in T1-T2 VDA performance • Number of license exam attempts
**Aim 3**. Identify age-related risk factors for crashes that may moderate the response to training	Interactions with Aim 1 & 2 outcomes	Interactions with Aim 1 & 2 outcomes

### Trial design

This trial uses random assignment with three parallel groups and follows an individually randomized group-treatment (IRGT) design. Participants are enrolled early in their learner permit and followed through licensure, and up to 6 months post-licensure, with the primary end point of crash risk at 2 months post-licensure. Participation length will vary with permit duration (range 8 to 18 months). After baseline, participants are randomized 1:1:1 to one of three groups (n = 333 per group): (i) professional BTW; (ii) ACCEL, a modern online driving skills training program; (iii) an active control online program covering vehicle safety topics without skills training. Participants in the BTW group will be clustered by instructor to account for variation in driver teaching style. Participants will be monitored remotely through the learner and post-licensure phases using surveys and a smartphone application capturing driving kinematics to quantify exposure and crash risk. At licensure, driving skill will be measured using three methods: the virtual driving assessment (VDA), an online hazard skills test, and results from the license examination. The primary endpoint is on-road kinematic crash risk (the rate of hard braking events) at 2 months post-licensure, with continued follow-up through 6 months post-licensure. Kinematic risky driving (KRD) events such as hard-braking events, have previously been validated as behavioral proxies for elevated crash risk [37–42]. See Fig. 1 and Table 2 for participant flow through the study and all procedures and measures through the trial.

**Fig. 1 Fig1:**
[figure not shown]
Flow diagram of participant progression through the trial, with participation estimated between 8–18 months (with varying learner/intervention phase)

**Table 2 Tab2:** Outline of the schedule of enrollment, interventions, and assessments

Timepoint	Enrollment	Baseline	Allocation	Intervention						Post-intervention	Post-Licensure		
	*-t*_*1*_	*t*_*1*_	*0*	*m*_*1*_	*m*_*2*_	*m*_*3*_	*m*_*4*_	*m*_*5*_	*m*_*6*_	*t*_*2*_	*m*_*8*_	*m*_*10*_	*m*_*12*_
Enrollment:	*X*												
Eligibility Screen	X												
Informed Consent/Assent	X												
Allocation to Trial Arm			X										
Interventions:													
Active Control Online Education				X	X	X	X	X	X				
ACCEL Online Driver Skills Training				X	X	X	X	X	X				
Behind-the-Wheel Training				X	X	X	X	X	X				
Assessments:													
Virtual Driving Assessment		X								X			
Penn Neurocognitive Battery		X											
Day-of-Performance Factors		X											
Driving Intake (status)		X											
Driving History (crashes/citations)		X		X	X	X	X	X	X	X	X	X	X
Personality Scales		X											
Demographic & Household Factors		X								X			
Adolescent Health Risk Factors		X											
Way to Drive Monitoring													
Driving Practice Quality Questionnaire				X	X	X	X	X	X	X			
Hazard Skills Test										X			
State Licensing Examination										X			
Driver Behavior Surveys										X	X	X	X

This table outlines the schedule of study procedures and provides an approximate length of participation, however, the intervention phase length will vary, and some drivers may need to retake the state license examination, extending the time before post-licensure follow-up. T1 and T2 = study assessment timepoints before and after the intervention learner permit phase; m = month

## Methods & analysis

This study is registered at ClinicalTrials.gov as of May 2024 (NCT06413927). Enrollment started in August 2024 and data collection is ongoing with an expected primary completion in December 2027, or until all final data collection is complete.

### Patients and population

The trial aims to enroll up to 1200 adolescent learner drivers with a goal of achieving 1000 evaluable participants, accounting for 20% attrition. Participants will primarily be recruited from primary care clinics in the Children’s Hospital of Philadelphia (CHOP) Network in the southeastern region of Pennsylvania (PA). The CHOP Network serves a heterogenous patient population: among patients age 16–17 years that visited a clinic at least once in the past 2 years, 33.7% are insured via Medicaid and the Children’s Health Insurance Program (CHIP); 49.4% are female sex; and approximately 47.9% are non-white. Potentially eligible adolescents will be identified through the electronic health record (under a waiver of HIPAA authorization for screening). Other eligible learner drivers who attend other Primary Care clinics and/or who respond to other recruitment and advertising strategies (e.g., study fliers) and who agree to travel to study locations for in-person procedures may also be enrolled.

#### Eligibility criteria

The eligibility criteria for this study include the following: participants must be aged 16–17 years, reside in PA, hold an active PA Learner’s permit with less than 30 h of driving practice (state requires 65 h before licensure), and have never taken a state driving licensing examination, and plan to get a license and to have access to a vehicle to drive after licensure. In addition, participants must have a personal cellphone, access to a smartphone/computer with internet access, and the ability to read and write in English to complete study tasks. Of note, prior research indicates that 95% of adolescents possess smartphones, with no significant differences by demographics [43]. Non-PA residents, non-English speaking participants, and those already enrolled in other learner driver studies will be ineligible.

### Intervention descriptions

All trial participants will receive care as usual, including information to access a Parents Supervised Driving Program from the Pennsylvania Department of Transportation (PennDoT), as well as information on how to access the PennDoT recommended smartphone app for logging practice hours (RoadReady App). In addition, one group will receive professional BTW with a local driving school instructor (6 h: 4 × 1.5 h lessons), another group will receive ACCEL online hazard skills training (~ 2 h), and another will receive an online active control vehicle and driver safety program (~ 2 h, with no skill training). While the ACCEL intervention is shorter than BTW instruction, this program is designed to be highly interactive and cognitively engaging, focusing specifically on the skill deficits that cause young driver crashes, and thus potentially offsetting the shorter duration. While the online programs can be completed in one sitting, participants can also take breaks and resume where they left off. Adherence (progress and duration) will be tracked via the e-learning platform (ScormCloud) event log and via a quiz and test at the end of the training. For BTW, driving instructors will fill out a brief post-lesson survey to confirm lesson content covered and completion.

#### In-person behind-the-wheel driver training (BTW)

Professional BTW will be carried out by a third-party accredited driver training school, and their partners. The driving school was chosen for its dual certification for training and license testing and is audited every 6–12 months, giving further support for the integrity of the intervention. The standardized curriculum used for the 6 h of training meets Pennsylvania and national standards, as reviewed by subject matter experts external to the study team from the PA Department of Education, Ohio Traffic Safety Office, and representatives of the American Driver and Traffic Safety Education Association (ADTSEA). Certified PA driving instructors will deliver the training, and school leadership will oversee fidelity through supervision, observations and end-of-lesson surveys completed in REDCap. Staff will also complete brief REDCap surveys (onboarding, post-lesson, offboarding) to monitor student progression and curriculum adherence.

#### Online driver skills training (ACCEL)

ACCEL [35] is an evidence-based online training program developed by [name] and colleagues at the University of Massachusetts Amherst. Designed to improve hazard anticipation, recognition, and attention maintenance, prior studies have shown ACCEL improves driving performance and reduces crash risk [31–33, 36]. For this trial, ACCEL was adapted for remote delivery to teen learner drivers by CHOP’s Department of Global Pediatric Education, with input from the CHOP Parent Family Education office to enhance health literacy. Pilot testing with local high school students informed revisions to language and graphics. The final version was reviewed and approved by the original developer, [name], and takes about 2 h to complete. In order to track remote adherence, progress and performance, this interactive training is hosted on SCORMCloud (by Rustici Software LLC), an online e-learning platform that can be accessed from any computer with internet access.

#### Active control: online vehicle and driver safety education

The active control group will complete an online video-based education program (~ 2 h) that covering vehicle maintenance and occupant safety (i.e., car seats, seat belts) but no driving skills training content. A short quiz at the end will confirm compliance. This program is also hosted on SCORMCloud which automatically tracks adherence, progress, and completion.

### Variables and outcome measures

Table 1 provides a summary of the study aims and outcomes. Table 2 summarizes all study procedures and measures.

#### Primary outcomes

There are two primary outcomes. First, crash risk in the first 2 months of licensure (Aim 1 and 3) will be measured as the rate of hard braking events per 100 miles driving, captured via the Way to Drive smartphone app. Monitoring of hard braking events will continue through 6 months to assess crash risk at 6 months also. The app, provided by Cambridge Mobile Telematics, deploys the same algorithms as leading usage-based automobile insurance programs to measure risky driving behaviors (phone use during trips, speeding, and other kinematic risky driving measures) [38]. Second, driver skills at licensure (Aim 2 and 3) will be measured as the pass rate on the first attempt of the state licensure examination. While the state licensing exam assesses a limited set of procedural driving skills, it provides a standardized, real-world benchmark of basic driving competence and is a relevant proximal outcome for novice drivers.

#### Secondary outcomes

Secondary outcomes include measures of risky driving behavior post-licensure. Self-reported crash involvement captured in follow-up surveys at 2-, 4- and 6-months post-licensure will provide a secondary outcome of crash risk. Self-reported risky driving behavior will also be captured in follow-up surveys. Other indicators of risky driving behavior post-licensure captured from the Way to Drive app include phone use while driving (number of minutes per hour driving) and speeding (proportion of driving at speed > 10 miles over the speed limit). Secondary outcomes of driver skills at the time of licensure will be measured via driver performance on the state licensing examination and change in performance class (pre- vs post-intervention) on the validated VDA [44, 45]. The number of license examination attempts and skills on the on-road examination will also be recorded as a secondary outcome.

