### Sample size

The target sample size for this randomized controlled trial is 1000 evaluable participants, with approximately 333 in each study arm (one group may include 334). This is based on the primary hypothesis of a reduction in hard braking events with driver training. The trial is powered to detect a 20% reduction in hard-braking events, a threshold identified by the U.S. Department of Transportation as predictive of reduced crash risk [57]. Additionally, it is designed to detect differences in state licensure exam pass rates between groups ranging from 15 to 19%, as well as an absolute increase of 10% to 13% in the proportion of drivers assigned to safer skill categories based on VDA classification. These thresholds reflect meaningful improvements in driving safety. A priori power analysis accounted for up to 20% attrition while maintaining 80% power to detect clinically meaningful effects, resulting in a worst-case scenario of 266 participants per arm. Retention strategies and participant replacement procedures are expected to mitigate attrition, leading to a final sample size of n = 800–1,000.

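### The simulated-driving (VDA) skill outcome is described inconsistently, and the 10 to 13 point detectable difference is not tied to either version; T2 class adjusted for T1 class should be the main analysis

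*Protocol article*

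**What the plan says.** The article describes the VDA outcome in four places.

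- Abstract, Methods: "change in simulated driving performance from baseline to the time of license examination". Only change is named.
- Objectives, Table 1, Aim 2 secondary outcomes: "Virtual Driving Assessment (VDA) Performance at T2" and, as a separate entry, "Change in T1-T2 VDA performance". Neither entry says whether performance means a class or a score.
- Secondary outcomes: "change in performance class (pre- vs post-intervention) on the validated VDA". Again only change is named, now in class.
- Sample size: the trial is said to be able to detect "an absolute increase of 10% to 13% in the proportion of drivers assigned to safer skill categories based on VDA classification". The paragraph claims this "while maintaining 80% power to detect clinically meaningful effects", "resulting in a worst-case scenario of 266 participants per arm".

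The Sample size section gives no control proportion, no correlation between the two assessments and no statement of which VDA outcome the figure describes. Statistical methods sets alpha at 0.05 and lists initial VDA class as a covariate, but only in a secondary analysis.

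**The concern.** T2 class and T1-T2 change in class can rank the same drivers differently. A learner in the safest class at both visits is in the favourable category at T2 but has not improved. If the text leaves open which is the main VDA result, the choice can be made after both are known.

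The power statement has the same gap. A proportion in safer categories reads most naturally as a T2 proportion, while two of the three places that name the outcome mention only change. Change carries the variability of both assessments. Unless they are well correlated, it needs a larger effect for the same power. The article gives the reader no way to tell whether its 80% applies to the outcome named in the Secondary outcomes section.

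**Working it through.** **Inputs from the article.** 333 per arm as target and 266 as worst case (333 × 0.8 = 266); 80% power; alpha 0.05. Two-sided testing is assumed, as are all class proportions and correlations. The VDA is treated as two levels (safer, less safe), with no clustering.

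**1. The stated 10 to 13 points.** Pooled two-proportion test at T2, difference detectable with 80% power:

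| Control proportion safer at T2 | 266 per arm | 333 per arm |
|---|---|---|
| 20% | 10.5 points | 9.3 points |
| 30% | 11.6 | 10.3 |
| 40% | 12.1 | 10.8 |
| 50% | 12.0 | 10.8 |
| 70% | 10.5 | 9.4 |

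The stated range is consistent with a T2 comparison. It cannot be traced to one set of inputs, because no control proportion is given. At alpha 0.025 and 266 per arm the range runs from 10.7 points (15% control) to 13.3 (40%).

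**2. One worked setting for change.** Assume 40% safer at T1 in both arms and, at T2, 50% in control and 63% in the trained arm (13 points), with 266 per arm.

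- T2 only: the variances sum to 0.50 × 0.50 + 0.63 × 0.37 = 0.4831. SE = √(0.4831/266) = 0.0426. Then 0.13/0.0426 − 1.96 = 1.09, giving 86% power.
- Change score: in each arm, variance = p₁q₁ + p₂q₂ − 2·cov(T1,T2). Without the covariance terms the two arms sum to 0.49 + 0.4731 = 0.9631. At a correlation of 0.40 in control (0.38 in the trained arm, from a common latent normal model) the covariances are 0.0987 and 0.0896. The sum becomes 0.9631 − 2 × 0.1883 = 0.5865, SE = 0.0470, and 0.13/0.0470 − 1.96 = 0.81, giving 79%.
- T2 adjusted for T1: the summed variance falls by (sum of covariances)²/(2 × 0.24) = 0.1883²/0.48 = 0.0739, to 0.4092. SE = 0.0392, giving 91%.

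| Correlation (control arm) | T2 only | Change score | T2 adjusted for T1 |
|---|---|---|---|
| 0.13 | 86% | 64% | 87% |
| 0.26 | 86% | 71% | 88% |
| 0.40 | 86% | 79% | 91% |
| 0.58 | 86% | 90% | 95% |
| 0.69 | 86% | 95% | 98% |

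**3. How far this depends on the assumptions.** With equal variances, the detectable difference on change is √(2(1−ρ)) times the T2-only one: 1.41 at ρ = 0, 1.18 at 0.3, 1.00 at 0.5 and 0.77 at 0.7. The starting proportions matter too (266 per arm):

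- T1 15%, control T2 25%, 13 points: change has 78 to 95% power at correlations 0.10 to 0.53.
- T1 10%, control T2 20%, 13 points: 84 to 96% at 0.09 to 0.50.
- T1 20%, control T2 20%, 10 points: 55 to 76% at 0.11 to 0.46, but T2 only is itself at 77%.

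**4. Why the adjusted analysis does not depend on the correlation.** Each comparison is a between-arm difference in T2 − b·T1: b = 0 for T2 only, b = 1 for change. Adjustment uses the b that minimises the residual variance, so in large samples it cannot do worse than either. With equal variances the factors are 1, 2(1−ρ) and 1−ρ². The last is never above 1. It also equals (1−ρ)(1+ρ), so it is never above 2(1−ρ).

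**5. Why the Sample size wording has to choose.** In the setting of step 2, a 13-point T2 effect produces a difference of only about 8 to 9 points in the proportion who improve (for example 23.7% against 31.9% at correlation 0.26), because drivers already safer at T1 cannot move up. A 10 to 13 point difference in improvers is therefore a different effect from the same difference at T2.

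**The case against.** The stronger readings do not hold. A reader might infer that the change outcome lacks the stated 80% power. The documents do not support that: the result turns on a correlation and on class proportions that the article does not give. Change overtakes T2 only in most settings once the correlation passes about 0.5. Entrants have under 30 hours of practice, so a low proportion in the safer classes at T1 is plausible, and there change keeps about 80% power or more at 13 points even with weak correlation. If the 10 to 13 points was meant as a difference in the proportion who improve, the ordinary two-proportion table in step 1 applies unchanged.

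A reader might also infer three conflicting definitions. That overstates it. Table 1, which the article names as its outcome summary, lists T2 performance and change as two outcomes. The abstract's list is not exhaustive, and the Sample size section states an effect rather than defining an outcome. Nor does the article define success as a yes/no improvement. How class is coded and modelled can properly sit in an analysis plan that is not shown.

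Finally, the baseline-adjusted model is already planned as a secondary analysis. All of this stands. What remains is that the Secondary outcomes section omits a Table 1 entry, class and performance are used interchangeably, the power figure is attached to neither outcome, and the analysis with the best precision is not the main one.

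**Conclusion.** The point holds as an inconsistency in how the VDA outcome is described, with a power figure not linked to a named outcome. The 10 to 13 points is consistent with a T2 comparison. For change, 80% power is not shown; it is not shown to be absent either. Under one assumed setting at 266 per arm and 13 points it runs from 64% at a correlation of 0.13 to 95% at 0.69. These figures rest on a two-level VDA, two-sided 0.05, no clustering and assumed proportions. The case for adjusting T2 class for T1 class does not depend on the unknown correlation.

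The severity is minor. The VDA is a secondary outcome and the sample size is based on hard braking events, so the trial's size is unaffected.

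**What to change.** Name one main VDA analysis: T2 class, as the proportion in the safer categories, compared between arms with T1 VDA class as a covariate. Report it as an absolute difference so that it stays on the scale of the power statement. Keep T1-T2 change as supportive or descriptive. Use the same wording in the abstract, Table 1 and Secondary outcomes, and move initial VDA class into the main model for this outcome in Statistical methods. In Sample size, state that the 10 to 13 points is the between-arm difference in the T2 proportion, and give the control proportion assumed.

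The cost is text, plus a matching registry entry if its wording differs. T1 class is already collected before allocation, so no new data are needed. Data collection is ongoing and no interim analyses are planned, so the change can be dated before the outcome comparison is seen. The one loss is that change is no longer a tested outcome of equal standing.
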